**Fecal sample**
The fecal sample will be analyzed for microbiome composition, inflammation markers, and other relevant indicators. The analysis will include assessing microbial diversity, identifying microbial species, measuring calprotectin levels as a marker of inflammation, analyzing cytokines, and evaluating digestive functions.d)
**Irritable Bowel Syndrome symptom severity**
The Irritable Bowel Syndrome-Symptom Severity Score (IBS-SSS) is a validated scale that assesses the severity and frequency of abdominal pain, severity of abdominal distention, dissatisfaction with bowel habits, and interference with quality of life over the past 10 days. Participants will respond to each question on a 100-point visual analogue scale, the range of the total score is 0-500.
^
48
^
e)
**Objective measurement using wearable device**
Wearable devices will provide objective and quantifiable data on various aspects, including the quality of sleep (sleep duration, sleep latency, and sleep efficiency), and physical activity (calories, step count, and active minutes).f
)
**Body-mind-spirit Well-being Inventory (BMSWBI)**
The Body-mind-spirit Well-being Inventory (BMSWBI) is a 56-item scale that assesses (1) physical distress, (2) daily functioning, (3) affect, and (4) spirituality. This outcome will only be measured among the level 3 participants.

### 2.7 Participant timeline

See
Table 3 and
Figure 3.

**Table 3. T3:** Details of assessments at each level of intervention.

Timepoint	A _1_bs_	A _2_bs_	A _3_bs_	A _1_imd_	A _2_imd_	A _3_imd_	A _1_6w_	A _2_6w_	A _3_12w_
**Enrolment**									
Informed consent	✓	✓	✓						
Demographic data	✓	✓	✓						
Medical history	✓	✓	✓						
Concurrent treatment	✓	✓	✓						
**Primary outcomes**									
PHQ-9	✓	✓	✓	✓	✓	✓	✓	✓	✓
GAD-7	✓	✓	✓	✓	✓	✓	✓	✓	✓
ISI	✓	✓	✓	✓	✓	✓	✓	✓	✓
**Secondary outcomes**									
SF-12	✓	✓	✓	✓	✓	✓	✓	✓	✓
PSS-10	✓	✓	✓	✓	✓	✓	✓	✓	✓
Utilization of healthcare resource	✓	✓	✓	✓	✓	✓	✓	✓	✓
TCM assessment	✓	✓	✓	✓	✓	✓	✓	✓	✓
Compliance rate				✓	✓	✓			
Adverse events				✓	✓	✓			
**Exploratory outcomes**									
Sample collection		✓			✓				
IBS-SSS		✓			✓				
Wearable device		✓			✓				
BMSWBI			✓			✓			✓

Note: A1_bs: Baseline assessment at level 1 intervention; A1_imd: Assessment immediately after level 1 intervention; A1_6w: Assessment 6 weeks after level 1 intervention; A2_bs: Baseline assessment at level 2 intervention; A2_imd: Assessment immediately after level 2 intervention; A2_6w: Assessment 6 weeks after level 2 intervention; A3_bs: Baseline assessment at level 3 intervention; A3_imd: Assessment immediately after level 3 intervention; A3_12w: Assessment 12 weeks after level 3 intervention. PHQ-9, Patient Health Questionnaire-9; GAD-7, General Anxiety Disorder-7; ISI, Insomnia Severity Index; SF-12, 12-Item Short Form Survey Instrument; PSS-10, Perceived Stress Scale-10; TCM, Traditional Chinese Medicine; IBS-SSS, irritable bowel syndrome-symptom severity score; BMSWBI, Body-mind-sprit Well-being Inventory.

**Figure 3. f3:**
[figure not shown]
Sketch map of assessments for 3 different levels of intervention. Note: A1_bs: Baseline assessment at level 1 intervention; A1_imd: Assessment immediately after level 1 intervention; A1_6w: Assessment 6 weeks after level 1 intervention; A2_bs: Baseline assessment at level 2 intervention; A2_imd: Assessment immediately after level 2 intervention; A2_6w: Assessment 6 weeks after level 2 intervention; A3_bs: Baseline assessment at level 3 intervention; A3_imd: Assessment immediately after level 3 intervention; A3_12w: Assessment 12 weeks after level 3 intervention. PHQ-9, Patient Health Questionnaire-9; GAD-7, General Anxiety Disorder-7; ISI, Insomnia Severity Index; SF-12, 12-Item Short Form Survey Instrument; PSS-10, Perceived Stress Scale-10; TCM, Traditional Chinese Medicine.

### 2.8 Sample size

We first estimated the sample size using the approach routinely employed in the standard randomized controlled superiority trial setting. Estimation of sample size was performed using G*Power 3.1.
^
49
^ Since there has been no study to evaluate the effectiveness of a stepped-care CHM intervention in patients with mild-to-moderate depression, anxiety, and insomnia, we conservatively estimated the effect size (Cohen’s d) of the intervention on the primary outcome is of small magnitude ~ 0.2.
^
50
^ Given the two-sided α of 0.05, power of 0.95, the sample size for a standard superiority RCT will be 260. Given the stepped wedge design of the present cluster randomized trial, we multiply the sample size by design effect which equals to 1+(m-1) x ICC, where m is the average cluster size and ICC is the intra-cluster correlation coefficient.
^
51
^ With reference to previous literature, the ICC equals to 0.01.
^
52
^ We operationalize the 18 districts in Hong Kong into 4 clusters, therefore the average cluster size m will be 260/4 clusters = 65. Thus, the design effect will be 1+(65-1) x 0.01 = 1.64. Therefore, the total sample size will be 260 x 1.64 = 428 (rounded up from 426.4). Considering the possibility of participant attrition during the 24-week study period, we have intentionally adopted a significant drop-out rate of 30% during the sample size calculation. This decision was made to ensure adequate statistical power.
^
53
^ As a result, the final sample size was determined to be 612 (428/0.7) participants.

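### The base sample size of 260 does not follow from the stated d = 0.2, two-sided alpha 0.05 and power 0.95, so the derivation does not support the claimed 95% power

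*Protocol article*

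**What the plan says.** All of this is in section 2.8 (Sample size) of the protocol article.

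- Starting point: "We first estimated the sample size using the approach routinely employed in the standard randomized controlled superiority trial setting".
- Software: "Estimation of sample size was performed using G*Power 3.1".
- Effect: the "effect size (Cohen’s d) of the intervention on the primary outcome is of small magnitude ~ 0.2", which the authors describe as a conservative choice.
- Result: "Given the two-sided α of 0.05, power of 0.95, the sample size for a standard superiority RCT will be 260".
- Use of the result: "therefore the average cluster size m will be 260/4 clusters = 65". The 260 is therefore a total, not a number per arm.
- Inflation: "With reference to previous literature, the ICC equals to 0.01", and "Thus, the design effect will be 1+(65-1) x 0.01 = 1.64". This gives 426.4, reported as 428, and then 612 after allowing for 30% dropout.

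The section names no statistical test, number of repeated measurements, within-person correlation, or conversion of d to another effect-size measure.

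**The concern.** The section gives everything needed to check its first step: design, effect size, alpha, sidedness, power and result. These do not fit together. Detecting 0.2 SD with 95% power in a two-arm trial takes well over a thousand participants, and 260 is about one fifth of that.

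This is more than detail condensed for a journal article, because the inputs and the output are both printed and are incompatible. It is also the only power statement in the document. A reader told that a conservatively small effect is detectable with 95% power would take a null result as strong evidence against even a small benefit. The Abstract says the results could guide integration of Chinese herbal medicine into mainstream care, so that reading could carry weight. The stated calculation gives it no basis.

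**Working it through.** **Inputs (all from section 2.8).** Standard superiority trial; d = 0.2; two-sided alpha 0.05; power 0.95; N = 260 in total. Equal allocation to two arms is my assumption, since no other ratio is given.

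**1. Required size from the stated inputs.** Normal approximation, per arm:

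n = 2 × (1.960 + 1.645)² / d² = 2 × 12.995 / 0.04 = 649.7, so 650 per arm and 1,300 in total.

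The exact noncentral-t calculation gives power 0.9498 at 650 per arm and 0.9501 at 651. The requirement is 651 per arm, 1,302 in total, and 1,302 / 260 is about 5.0.

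**2. Power at the stated size.** With 130 per arm the noncentrality is 0.2 × √(130/2) = 1.61, against a critical value of about 1.97. Exact power is 36%. The effect detectable with 95% power is about 3.605 / √65 = 0.447 by normal approximation, or 0.449 exactly, so d is about 0.45.

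**3. Other readings of the same inputs.**

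| Reading | Result |
|---|---|
| 260 per arm instead of total | power 62% |
| One-sided, power 0.95 | 1,084 |
| Two-sided, power 0.90 | 1,052 to 1,054 |
| Two-sided, power 0.80 | 786 to 788 |
| Paired, two-sided, power 0.95 | 327 |
| Paired, one-sided, power 0.95 | 272 |
| Paired, two-sided, power 0.90 | 265 |

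The last row comes close, but it has neither the stated power nor a two-group comparison. A change-score analysis reaches 260, and baseline adjustment reaches 248, only with a baseline correlation of 0.9, which the document does not assume.

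**4. A route that does give 260 (inference only).** Take the G*Power repeated-measures ANOVA, within-between interaction, with f = 0.10, 2 groups, 3 measurements and correlation 0.5. The noncentrality is λ = f² × N × 3 / (1 − 0.5).

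- N = 258: λ = 15.48, power 0.949.
- N = 260: λ = 15.60, power 0.951.

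This fits exactly, and f = 0.10 is d/2 for d = 0.2. But d/2 is the conversion for two group means at one time, not for an interaction. Suppose the groups are equal at baseline and differ by δ at both later visits. The interaction terms are then ∓δ/3, ±δ/6 and ±δ/6, so

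f² = (δ²/9 + δ²/36 + δ²/36) / 3 = δ²/18.

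Setting f = 0.10 gives δ = 0.1 × √18 = 0.42 SD. Conversely, δ = 0.2 gives f = 0.047. At 260 and correlation 0.5 that is 36% power, and 1,160 participants would be needed for 95%. With correlation from 0.3 to 0.8, power at 260 runs from 27% to 75%.

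**5. What rests on 260.** 260 / 4 = 65; 1 + 64 × 0.01 = 1.64; 260 × 1.64 = 426.4; 428 / 0.7 = 611.4, rounded up to 612. These steps are arithmetically sound, except that 426.4 rounds up to 427, not 428, which is immaterial. I have not assessed here whether the design-effect formula suits a stepped-wedge trial.

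**The case against.** **260 is probably not a random slip.** The repeated-measures route reproduces it exactly, and Table 3 schedules three assessments at each treatment level. That stands as a plausible origin, so it would be too much to say that 260 can have no derivation. It does not rescue the statement. The test, number of measurements, correlation and f are all undeclared, and under the effect pattern in the working f = 0.10 is not a 0.2 SD difference. The 0.42 SD depends on that assumed pattern and is illustrative.

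**The trial is not a two-arm parallel trial of 260.** This also stands. A reader might infer that the study has 36% power or is five times too small. The documents do not support that, because those figures check a printed intermediate step. The trial targets 612 participants in a stepped-wedge design with repeated assessments.

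**Recomputed power need not be worse.** A reader might infer that an honest figure must fall well below 95%. That is not established either. Illustrative stepped-wedge calculations for about 430 analysed participants run from about 26% to 97%. The result depends on how time is modelled, whether a participant effect is included, and the within-person correlation. Those settings are assumptions that the documents do not fix, so the range shows sensitivity and is not an estimate.

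**The consequence is limited.** Section 2.1 says recruitment is complete, and the error biases neither the effect estimate nor its confidence interval. That is true. It bears on the cost of the remedy and not on whether the statement is correct.

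**Conclusion.** The point holds as a mismatch between stated inputs and stated result. For d = 0.2, two-sided alpha 0.05 and power 0.95, a two-arm superiority trial with equal allocation needs about 1,302 participants, not 260. At 260 the power is about 36%, and 95% power applies only to d of about 0.45. Since 428 and 612 descend from 260, the claim of 95% power at d = 0.2 is unsupported by the derivation given.

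This rests on section 2.8's own figures and on its use of 260 as a total. The equal-allocation assumption is not critical, because unequal arms would need more participants. The power of the actual trial remains undetermined from the document. The statement should be corrected because it is the trial's only power claim and correcting it is cheap.

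**What to change.** Withdraw the statement that 260 gives 95% power for d = 0.2, together with the chain from 65 to 612 as a justification of power. The 612 can remain as the recruitment target that was set.

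Replace it with a stepped-wedge calculation for the achieved sample under the planned analysis model. It should use the 18 districts, the four sequences with their actual district counts, the real visit schedule, the ICC, and a stated range of within-person correlation and cluster autocorrelation. Report power at d = 0.2, or the effect detectable at 80% and 95% power, whichever way the result falls. If a repeated-measures calculation did produce 260, say so and give its inputs.

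The cost is one calculation and a text correction, with no extra enrolment.

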**Methods:**

This study will be a multicenter, pragmatic stepped-wedge cluster randomized trial. Districts will be randomized to receive the CHM intervention sequentially in four steps based on a computer-generated number, while control districts remain unexposed until their respective intervention phase. The intervention consists of a three-level stepped-care approach: Level 1 involves herbal tisane for mild symptoms, Level 2 offers standardized CHM for moderate symptoms or non-responders to Level 1, and Level 3 combines personalized CHM with psychotherapy for those not improved by Level 2. Symptom severity will be assessed using validated scales, Patient Health Questionnaire-9 for depression, Generalized Anxiety Disorder-7 for anxiety, and Insomnia Severity Index for insomnia, with primary outcomes measured at baseline, post-intervention, and follow-up. The study was approved by the Hong Kong Baptist University Research Ethics Committee (Approval No.: REC/22-23/0709).

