### 2.15 Statistical methods

Data will be presented as mean (standard deviation) or frequency (percentage). The Hussey-Hughes model will be utilized for data analysis, where linear mixed models will be used for continuous outcomes, and generalized estimating equations will be used for categorical outcomes. Pairwise comparisons will be performed using linear contrast. Statistical significance will be considered at p < 0.05. The Holm procedure will be applied to address multiplicity. All statistical analyses will be performed using SAS OnDemand for Academics. All outcomes will be statistically analyzed according to the intention-to-treat principle and the per-protocol population separately.

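### The 0.95 power in section 2.8 is for one primary outcome at unadjusted two-sided 0.05, but three scales are primary and Holm is planned, so it does not describe the power for a given scale if Holm spans the three

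*Protocol article*

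**What the plan says.** Section 2.8 (Sample size) takes an effect "of the intervention on the primary outcome is of small magnitude ~ 0.2" on Cohen's d, in the singular. It continues, at a two-sided alpha of 0.05: "power of 0.95, the sample size for a standard superiority RCT will be 260". The later steps (design effect 1.64, 30% dropout, final N of 612) carry that figure forward with no allowance for more than one primary test.

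Section 2.6 (Outcomes), Table 3 and the Abstract give three primary outcomes: "Patient Health Questionnaire-9 for depression, Generalized Anxiety Disorder-7 for anxiety, and Insomnia Severity Index for insomnia".

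Section 2.15 (Statistical methods) says "Statistical significance will be considered at p < 0.05" and then "The Holm procedure will be applied to address multiplicity". It does not say which tests form the Holm family. No section says whether success means an effect on one scale, on each scale judged separately, or on all three.

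**The concern.** The sample-size section and the analysis section use different significance levels. Section 2.8 credits the trial with 95% power for a single test at 0.05. If Holm is run over the three primary scales, the smallest p-value is compared with 0.05/3 = 0.0167, the next with 0.05/2 = 0.025, and only the largest with 0.05. A given scale is then tested at 0.05 only if both others have already been rejected.

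At stake is the accuracy of a stated design figure. A reader who sets a non-significant scale against 95% power would assume a 5% chance of missing the assumed effect, and under the planned adjustment that chance can be about 11%. Unequal effects across the scales are plausible here. Section 2.3 admits participants who meet the score range on any one of the three scales, and the Level 1 tisanes in section 2.5.2 are specific to the main complaint.

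**Working it through.** **Inputs.** From section 2.8: d = 0.2, two-sided alpha 0.05, power 0.95, N = 260 before design effect and dropout. From section 2.6: three primary scales. From section 2.15: Holm. Assumed, because the protocol does not give them: the Holm family is the three primary scales; correlation between the scales' test statistics is 0 to 0.9; a scale that benefits does so by d = 0.2; allocation is 1:1 for the two-sample check.

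**Step 1. Reproduce 260.** For two independent means, total N = 4 × ((1.960 + 1.645)/0.2)² ≈ 1,300, that is 650 per arm. This is not 260. With 260 in total, the noncentrality is 0.2 × √(260/4) = 1.612, and power is about 0.36 at 0.05 and about 0.22 at 0.0167. A paired two-sided comparison needs 325. The figure of 260 is matched exactly by a repeated-measures F test with f = 0.1, two groups, three measurements and correlation 0.5 (power 0.951), but the protocol states none of these settings. The premise that 260 gives 95% power is therefore undocumented. The steps below grant it only to isolate the effect of Holm.

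**Step 2. Power for one test at each Holm threshold.** A test with 95% power at two-sided 0.05 has noncentrality 1.960 + 1.645 = 3.605.

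| Threshold | Critical value | Power |
|---|---|---|
| 0.05 | 1.960 | Φ(3.605 − 1.960) = 0.950 |
| 0.025 | 2.241 | Φ(3.605 − 2.241) = 0.914 |
| 0.0167 | 2.394 | Φ(3.605 − 2.394) = 0.887 |

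The repeated-measures reading of 260 gives nearly the same at 0.0167 (0.889). The effect detectable with 95% power at 0.0167 is 0.2 × (2.394 + 1.645)/3.605 = 0.224.

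**Step 3. The full Holm procedure.** This was simulated with three correlated z-tests, noncentrality 3.605 for each scale that benefits and 0 for the others, at correlations 0, 0.3, 0.5, 0.7 and 0.9.

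| Scales that benefit | Power for a given benefiting scale |
|---|---|
| One | 0.887 to 0.890 |
| Two | 0.90 to 0.91 |
| All three | 0.94 (correlation 0) to 0.92 (correlation 0.9) |

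When all three benefit:

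| Correlation | At least one scale | All three scales |
|---|---|---|
| 0 | 0.999 | 0.854 |
| 0.3 | 0.991 | 0.864 |
| 0.5 | 0.981 | 0.872 |
| 0.7 | 0.964 | 0.887 |
| 0.9 | 0.935 | 0.903 |

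**The case against.** Four points on the other side deserve weight.

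- **The stated power can be met.** A reader might infer that 0.95 holds only for one unadjusted test. That is too strong. If success means at least one scale and all three benefit, power is 0.96 or more up to correlation 0.7. The protocol states no success rule, so the shortfall applies to power for a given scale and to power for all three, not to every reading. This stands.
- **The Holm family is not named.** In section 2.15 the Holm sentence comes after one on pairwise contrasts, so it could cover those contrasts, the three scales or all outcomes. Naming the family can be left to an analysis plan that is not shown, and its absence is not the fault raised here. The figures are therefore conditional. Three scales listed side by side as primary make the three-scale family the natural reading, and a larger family that includes them would lower power further.
- **The figure of about 0.89 is the least favourable per-scale case.** It needs exactly one scale to benefit. When all three do, a given scale loses only about 1 to 3 points. A reader might be tempted to print about 89% as the corrected power. The documents do not support that: it is one scenario, and it presupposes that 260 gives 95% power, which the stated inputs do not.
- **The unexplained 260 is the larger fault in the same sentence.** This is true. Repairing it alone, however, would still leave a power figure at an alpha that differs from the planned analysis.

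It is also fair that no section uses the 95% to interpret a null result. The consequence described is for a later reader, not something the protocol does.

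**Conclusion.** The point holds in conditional form. The 0.95 in section 2.8 belongs to a single outcome at unadjusted 0.05, and the planned analysis has three primary scales with Holm. If Holm covers those three, and granting the 95% premise, power for a given scale is lower than stated by about 6 points at worst and about 1 point at best. The chance of showing all three is about 5 to 10 points below 0.95.

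This rests on the three-scale family, equal effects of d = 0.2 on the scales that benefit, and assumed correlations of 0 to 0.9. It does not show that the trial is underpowered under every success rule, and it does not establish 89% as the trial's actual power. It shows that a stated design figure does not match the alpha the plan would use, and that no replacement can be trusted until the basis of 260 is documented. The correction is worth making and is modest in size.

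**What to change.** No change in N; section 2.1 reports recruitment as complete. In this order:

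1. In section 2.8, document the test, number of measurements and correlation behind 260, or recalculate the power that the planned N gives.
2. In section 2.15, name the three primary scales as the Holm family, and state whether success means one, each or all of them.
3. In section 2.8, replace the 0.95 with the power at the Holm thresholds under that rule, giving the assumed correlation range and how many scales are assumed to benefit. Print a figure of about 0.89 only if step 1 shows that the 95% premise holds.

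The cost is a few sentences in the protocol or analysis plan, best added before outcome data are examined. The downside is a less favourable stated power.

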## 2. Methods

### 2.1 Trial design

This interventional study will be a multicenter, pragmatic, stepped-wedge, cluster randomized trial. Randomization will be carried out based on the 18 geographic districts in Hong Kong. The CHM intervention will be sequentially implemented in 4-6 districts per step according to a computer-generated random number while the remaining clusters will continue to stay unexposed to the intervention. After a 4-step exposure, all districts will receive the CHM intervention (
Figure 1). The study was approved by the Hong Kong Baptist University Research Ethics Committee (Approval No.: REC/22-23/0709) on April 8, 2024, and prospectively registered with the Chinese Clinical Trial Registry (ChiCTR2400083685) on April 30, 2024,
https://www.chictr.org.cn/hvshowprojectEN.html?id=251238&v=1.0. Recruitment started on May 1, 2024, and has already been completed. Data collection is expected to end in July 2025. The study is conducted according to the guidelines for good clinical practice (ICH/GCP) and the Declaration of Helsinki.
^
40
^ This protocol strictly adhered to the Standard Protocol Items: Recommendations for Interventional Trials (SPIRIT) 2013 statement (
**refer to data availability**).

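### Section 2.8 computes the design effect with 4 clusters, a pre-inflation cluster size and a parallel-trial formula, so 428 and 612 follow neither from the 18 randomised districts nor from 4 clusters

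*Protocol article*

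**What the plan says.** Protocol article, section 2.1, on the randomised unit: "Randomization will be carried out based on the 18 geographic districts in Hong Kong". The note to Figure 1 and section 2.10 agree: districts are randomised, 4 to 6 of them start at each step, and after four steps all are exposed.

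Section 2.8 starts from an individually randomised trial: "Given the two-sided α of 0.05, power of 0.95, the sample size for a standard superiority RCT will be 260". It then adjusts for the design: "we multiply the sample size by design effect which equals to 1+(m-1) x ICC, where m is the average cluster size". The ICC is fixed: "With reference to previous literature, the ICC equals to 0.01". The number of clusters enters here: "We operationalize the 18 districts in Hong Kong into 4 clusters, therefore the average cluster size m will be 260/4 clusters = 65". From these the section obtains a design effect of 1.64, a total of 428, and 612 after 30% dropout.

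Section 2.15 plans a Hussey-Hughes analysis, with linear mixed models for continuous outcomes and generalised estimating equations for categorical ones.

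**The concern.** Three choices in section 2.8 do not fit the design described elsewhere in the article.

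- **Unit.** Section 2.8 counts 4 clusters where 18 districts are randomised. Four is the number of steps.
- **Cluster size.** The formula needs the size of the clusters in the trial that will be run. Section 2.8 uses 260/4, the size before the design effect is applied.
- **Formula.** The expression is introduced as the adjustment for the stepped-wedge design, but it is the inflation for a parallel cluster trial. It has no term for steps, periods or crossover within a cluster, and the variance in a Hussey-Hughes model depends on these.

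At stake is whether 428 analysed participants (612 recruited) deliver the stated 95% power. A reader cannot tell from the calculation as given.

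**Working it through.** **Inputs, all from section 2.8 unless noted:** base n = 260; ICC = 0.01; dropout 30%; 4 clusters (section 2.8) or 18 districts (section 2.1).

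**1. The plan's own figures.** m = 260/4 = 65. Design effect (DE) = 1 + 64 x 0.01 = 1.64. 260 x 1.64 = 426.4, stated as 428 (plain rounding up gives 427; the difference is trivial). 428/0.7 = 611.4, so 612. The arithmetic reproduces; the fault is in the inputs and the formula.

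**2. Does 428 meet the target of 260?** Effective n = N / [1 + (N/K - 1) x ICC], where K is the number of clusters.

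- K = 4: m = 428/4 = 107, DE = 2.06, effective n = 428/2.06 = 208.
- K = 18: m = 428/18 = 23.8, DE = 1.228, effective n = 428/1.228 = 349.

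**3. What the same formula requires.** With m set to the actual size N/K, solving N = 260 x [1 + (N/K - 1) x ICC] gives N = 260(1 - ICC) / (1 - 260 x ICC/K).

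| Clusters | How m is set | N | After 30% dropout |
|---|---|---|---|
| 4 | 260/4 = 65 (as stated) | 426.4, given as 428 | 612 |
| 4 | actual size | 257.4/0.35 = 735.4, so 736 | 736/0.7, about 1,052 |
| 18 | 260/18 = 14.4, DE 1.134 | 295 | 422 |
| 18 | actual size | 257.4/0.8556 = 300.9, so 301 | 430 |

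The stated figures are about 42% to 45% above the 18-district results (428 against 301 to 295) and about 42% below the self-consistent 4-cluster result (428 against 736).

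**4. Dependence on the ICC.** With 4 clusters and a base of 260, no cluster size reaches the target once the ICC is 4/260 = 0.0154 or more. With 18 districts, 428 still meets 260 while 1 + 22.78 x ICC is at most 428/260 = 1.646, that is, up to an ICC of about 0.028.

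**5. A stepped-wedge design effect, for illustration only.** Assumptions not in the article: a new cross-section of n people per cluster in each of 5 periods (one control period, then four steps). Then DE = [1 + ICC(5n - 1)] / [1 + ICC(3n - 1)] x 3(1 - ICC) / [2(4 - 1/4)], and total observations = 260 x DE x 5.

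- K = 18: n = 6.33, DE = 0.4385, about 570 observations before dropout.
- K = 4: n = 34.5, DE = 0.531, about 690 observations before dropout.

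These count observations, not people followed over time, so they cannot replace 428. They show that the parallel formula is not a stand-in for a stepped-wedge one.

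**6. Power, conditionally.** The origin of 260 is not stated. It is reproduced exactly by a repeated-measures interaction test with f = 0.1, 2 groups, 3 measurements and correlation 0.5. If that was the method, effective sizes of 208 and 349 correspond to power of about 0.89 and 0.99.

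**The case against.** The strongest reply is that the error is harmless or even cautious. If the district is the cluster, as sections 2.1 and 2.10 say, 428 exceeds the 295 to 301 that the plan's own formula needs. The large figures, 736 and about 1,052, arise only under a cluster definition that the rest of the article does not use. Section 2.8 also states its grouping into 4 openly, and recruitment is complete. On direction this stands, given 260 and an ICC near 0.01. It does not rescue the calculation: declaring the grouping does not make steps into randomised units, and a formula without periods or crossover does not establish the power of a stepped-wedge analysis.

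A reader might infer that the analysis itself will rest on four units, with the unreliable random effects and standard errors that would follow. The article does not support that. The 4-cluster wording occurs only in section 2.8. Section 2.15 names Hussey-Hughes without specifying four units, and section 2.1 treats districts as the clusters. Small-sample corrections may properly sit in an analysis plan that is not shown.

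A reader might also infer that repeated scores on the same person were ignored throughout. That is not established either: the match in step 6 means they may already be in the 260.

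Finally, a definitive stepped-wedge figure needs inputs the article does not give: the sampling scheme, participants per period and the within-person correlation. Table 3 schedules assessments relative to each treatment level, not by calendar period. This stands, and it limits the remedy to a recalculation under declared assumptions.

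**Conclusion.** The point holds as an internal inconsistency in the sample-size inputs and formula, not as a slip in the printed arithmetic. The figures 428 and 612 follow under neither cluster definition.

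It is tempting to conclude that the trial is underpowered, but the calculation does not show that. On the plan's own formula the effective size is about 349 with 18 districts and about 208 with 4 clusters, against 260. Since districts are what is randomised, the parallel formula errs on the cautious side at the stated ICC. What fails is the support for the stated sample size and 95% power.

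These results take 260 and ICC = 0.01 at face value. The base is a separate question: a plain two-group comparison at the stated effect size of about 0.2 with 95% power needs about 1,300 in total, so any reassurance from 349 against 260 depends on how 260 was obtained.

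**What to change.** - In section 2.8, and in the description of the model in section 2.15, define the cluster as the district (18), and describe the four groups as sequences.
- Replace 1+(m-1) x ICC with m = 65 by a stepped-wedge variance consistent with the Hussey-Hughes analysis, using 18 districts in 4 sequences. State the sampling scheme, participants per period, within-person correlation and ICC as assumptions, and show the result over a range of each.
- Restate the power of the sample actually recruited in place of the claim that 428 (612 with dropout) gives 95%.

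The cost is a text change and a recalculation, best done before the data are analysed. Recruitment is already complete and is not affected.
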